### Data analysis

In respect of the bespoke questionnaire on usability and acceptability, categorical variables will be described in frequencies and percentages, while mean scores will be reported for the incorporated Systems Usability Scale and UMUX-Lite. 

The audio-recorded semi-structured interviews will be transcribed verbatim. Transcripts of the interviews will be anonymised and the audio-recordings will be destroyed immediately following transcription. Transcripts will be read and re-read to ensure data immersion. Thematic analysis will be undertaken using open coding to identify patterns and themes in a six-stage process involving: familiarisation, generating initial codes, developing themes, reviewing themes, defining and naming themes, and reporting findings
^
46
^. This process of analysis will be undertaken manually at first and then repeated using a qualitative data management software system to ensure thorough analysis. Emerging patterns and themes will be discussed periodically amongst all the researchers involved in this study (except [name] – see competing interests statement below) to facilitate collaborative reflexive analysis as consensus is reached
^
58
^. The Standards for Reporting Qualitative Research will be adhered to when reporting the findings of the study
^
59
^.

### Discussion

This mixed-methods study will explore the usability and acceptability of a dCBT-I (
*Sleepio*) intervention in people with cognitive impairment. CBT-I is the first-line treatment for insomnia
^
30–
33
^. However, the effectiveness of cognitive behavioural therapy may be limited in people with cognitive impairment by their diminished ability to comprehend, learn, remember and apply the skills taught by the therapy programme
^
48
^. This may be more marked for dCBT-I. By including participants with cognitive impairment ranging from SCD to mild-moderate dementia, this study will help identify the categories of people from amongst this cohort who are most likely to benefit from dCBT-I. By examining the barriers and facilitators that influence usability and acceptability of the
*Sleepio* programme amongst people with cognitive impairment, this study will investigate how the delivery of dCBT-I may be adapted to enhance usability and acceptability amongst this population. In particular, the effect of digital literacy and the availability of study partners to support adherence to the programme will be analysed. Improved understanding of the influence of these factors will assist in the development of guidance on the use and application of dCBT-I in clinical practice for this cohort and older adults in general, who often rate their own comfort and familiarity with technology as poor or average
^
60
^. By providing insights into the factors that influence usability, acceptability and potential efficacy of dCBT-I amongst people with cognitive impairment, this study will also help inform the design of a future definitive randomised controlled trial that will assess the effectiveness of dCBT-I to treat probable insomnia amongst this population.

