## Aim

Given the importance of treating co-morbid sleep disturbance at all stages of cognitive decline, we propose to undertake a mixed-methods analysis of the usability and acceptability of dCBT-I (
*Sleepio*) among people with varying degrees of cognitive decline, ranging from subjective cognitive decline (SCD) through to MCI and mild-moderate dementia. We will also endeavour to assess whether usability and acceptability can be improved by the availability of a study partner to assist with operation of the dCBT-I (
*Sleepio*) programme. This will help to determine which people with cognitive impairment may be able to use and benefit from dCBT-I (
*Sleepio*) to treat co-morbid sleep disturbance.

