## Methods

### Intervention

*Sleepio* is a fully-automated and personalised dCBT-I intervention designed to treat insomnia using a combination of cognitive, behavioural, sleep hygiene and relaxation techniques. It is delivered through a web-based platform, supporting iOS or Android mobile applications. Underlying algorithms organise the delivery of information, support, and advice in a manner tailored to each individual patient based on their responses to an initial sleep study questionnaire and subsequent daily sleep diary entries throughout the duration of the programme. The programme consists of six sessions, each between five and twenty minutes in duration.
*Sleepio* can be completed within a six-week period. However, the average time taken to complete the programme is 9–10 weeks. No time restriction is placed on the user to complete the sessions, and all previously viewed sessions remain available to the user to re-watch throughout the duration of the programme. Participants are offered daily notifications to prompt adherence to the programme.

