### Participants

Potential participants will be community-dwelling adults aged fifty years and older with probable insomnia attending outpatient memory clinics affiliated with the Mercy University Hospital in Cork, Ireland. Only participants with probable insomnia will be included because, although previous studies have suggested the effectiveness of
*Sleepio* in sub-clinical insomnia
^
47
^, other studies have demonstrated that participants’ motivation to adhere to the
*Sleepio* programme was proportional to the severity of their sleep disturbance
^
43
^. Study partners, if available, will also be recruited for dyadic participation and may include caregivers, family members or friends attending memory clinic with the participants. A previous qualitative study of the usability of
*Sleepio* amongst patients following stroke found that some had to rely on help from partners to operate the programme and suggested that more people may be able to use dCBT-I if given support from a partner or caregiver
^
43
^. It is anticipated that study partners may play an important role in facilitating successful adherence of participants to the
*Sleepio* programme, particularly among participants with more advanced cognitive impairment
^
48
^. While ideal and likely to enrich the study, the availability of a study partner will not be an inclusion/exclusion criterion. We will nevertheless endeavour to include them when available. Other inclusion/exclusion criteria are as follows:

Inclusion criteria:

1. Aged ≥50 years.2. Sleep Condition Indicator (SCI)
^
49
^ Score ≤16/32. The SCI is an 8 item scale validated to assess insomnia based on DSM-5 criteria. Scores range from 0–32, with scores ≤16 indicating probable insomnia.3. Established SCD, MCI or mild-moderate dementia, diagnosed by a consultant physician specialised in cognitive disorders prior to enrolment in the study. Dementia will be defined using DSM-5 classification and staged according to the Reisberg FAST scale
^
50
^ into early/mild/moderate stage. MCI will be defined using Petersen’s criteria
^
51
^. Participants must score between 0 – 2 on the Clinical Dementia Rating (CDR) scale
^
52

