### Recruitment

All patients attending memory clinics affiliated with the Mercy University Hospital in Cork, Ireland will be screened for eligibility. Consecutive patients who meet eligibility criteria will be invited to participate in the study. It is hoped to recruit 20–30 participants over a four month period. Where possible, study partners including friends or family members of participants, will be recruited to support participants throughout the study.

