### Enrolment

Once recruited, participants will be provided with access to the study intervention (
*Sleepio*). Given the digital nature of the intervention, each participant’s digital literacy will be assessed using the Mobile Device Proficiency Questionnaire
^
53
^. Every participant will be provided with a training/orientation session to teach them how to use the
*Sleepio* programme. Additionally, each participant will be provided with clear written instructions on how to access and use the
*Sleepio* programme. If a study partner is available, and both the participant and the study partner consent to their participation in the study, the partner will be also included in the training session.

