### Data collection

Data collection will be carried out in accordance with the European Union’s General Data Protection Regulation and local data protection policies. The following data will be recorded in respect of every participant at baseline:

Demographic data, including: age, sex, marital status, level of education, and employment status.Charlson Co-morbidity Index
^
54
^
Cognitive diagnosis and stage of cognitive impairmentMedications

Following completion of the
*Sleepio* programme, usability and acceptability will be assessed initially by a bespoke questionnaire incorporating the System Usability Scale
^
55
^, adapted for cognitive impairment
^
56
^, and the Usability Metric for User Experience - Lite (UMUX -Lite)
^
57
^. The System Usability Scale is a validated and commonly employed 10 item Likert-type scale that provides a global assessment of how user-friendly a system or product is perceived to be. The UMUX-Lite is a more condensed two item Likert-type scale that also measures user-satisfaction with a system or product. Finally, participants and their study partners (where applicable) will be interviewed to further assess the usability and acceptability of the programme. The interview will be audio-recorded and conducted in a semi-structured manner using the topic guide included in the supplementary material. Participants and their study partners will be asked to expound on any difficulties they had in complying with the programme and whether they found the programme beneficial. In order to reduce the possibility of social desirability and positivity bias, the participants and their study partners (where applicable) will be informed that the interviewer is not affiliated with
*Sleepio* and that the objective of the study is to obtain an accurate understanding of their experience using the programme in order to guide future research.

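### The article promises to analyse digital literacy and partner support for adherence, but names no completion or usage measure, no analysis by either factor, and no assessment of people who stop early

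*Protocol article*

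**What the plan says.** The Discussion of the protocol article says that "the effect of digital literacy and the availability of study partners to support adherence to the programme will be analysed". The Aim section puts the partner question in terms of usability and acceptability: the study will "assess whether usability and acceptability can be improved by the availability of a study partner to assist with operation" of the programme. The Participants section gives the expected mechanism, namely that "study partners may play an important role in facilitating successful adherence of participants to the" programme.

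One explanatory factor is measured. Under Enrolment, "digital literacy will be assessed using the Mobile Device Proficiency Questionnaire". Partners are recruited where available and are not required for entry.

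Under Data collection, "The following data will be recorded in respect of every participant at baseline" introduces demographics, the Charlson index, cognitive diagnosis and stage, and medications. Once the programme is completed, "usability and acceptability will be assessed initially by a bespoke questionnaire incorporating the System Usability Scale" and the UMUX-Lite. Semi-structured interviews with participants and partners follow, and these include questions on difficulties in complying.

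Data analysis provides for frequencies and percentages for categorical items, mean scores for the two scales, and thematic analysis of the transcripts.

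**The concern.** The analysis announced in the Discussion has no counterpart in the two sections that should support it. No variable records how far a participant got, and no outcome is set against digital literacy or partner status.

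The timing adds to this. The questionnaire and interview come after completion, and the Intervention section sets no limit on how long a participant may take. Someone who stops at session two never reaches the stated assessment point. That person is among the most informative for a study of who can use the programme, especially at the more impaired end of the range.

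The study is meant to show which people with cognitive impairment can use the programme and to inform a later randomised trial. A good mean usability score is hard to interpret for either purpose if the reader cannot tell whether it comes from nearly everyone enrolled or from a selected group who finished.

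**Working it through.** The article states no power, error rate, effect size or completion rate, so there is no figure to reproduce. The check sets the promise against the data and the analysis.

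**Step 1: promise against plan**

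| Element needed | Where it would appear | What the article names |
|---|---|---|
| Digital literacy | Enrolment | Mobile Device Proficiency Questionnaire |
| Partner status | Participants, Enrolment | Known from recruitment |
| Usability and acceptability scores | Data collection | System Usability Scale, UMUX-Lite |
| Adherence, qualitative | Data collection | Interview questions on difficulties in complying |
| Sessions completed, diary use, last use, dropout | Data collection | None |
| Any outcome described by digital literacy or partner status | Data analysis | None |
| Assessment of people who stop early | Data collection | None |

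The explanatory factors and the self-report outcomes exist. Objective completion or usage variables named: 0. Analyses by either factor named: 0.

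**Step 2: is there something to record?** The Intervention section describes six sessions and tailoring based on "subsequent daily sleep diary entries throughout the duration of the programme". Sessions completed therefore has a natural scale of 0 to 6. The article does not say whether investigators can obtain the programme's records.

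**Step 3: what a completion rate would add.** Intervals are exact (Clopper-Pearson). For x completers of n, the lower limit is the 2.5% quantile of Beta(x, n−x+1) and the upper limit is the 97.5% quantile of Beta(x+1, n−x).

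The Introduction reports that in a stroke study 9 of 11 completed the programme, three of them with caregiver help, so 9 − 3 = 6 of 11 completed unaided. The Recruitment section hopes for 20 to 30 participants. The 80% in the last three rows is my assumption for illustration; it is close to 9/11 = 82%.

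| Case | Proportion | Exact 95% CI |
|---|---|---|
| Stroke study, completed | 9/11 = 82% | 48–98% |
| Stroke study, completed unaided | 6/11 = 55% | 23–83% |
| Assumed 80%, n=20 | 16/20 | 56–94% |
| Assumed 80%, n=25 | 20/25 | 59–93% |
| Assumed 80%, n=30 | 24/30 | 61–92% |

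The planned sample would give a usefully tighter estimate than the stroke study, in the population of interest.

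**Step 4: effect of assessing completers only.** Let p be the proportion completing. The mean score over all enrolled is p × (completer mean) + (1 − p) × (non-completer mean). The completer mean therefore exceeds it by (1 − p) × (completer mean − non-completer mean). With p = 9/11, 1 − p = 2/11 = 0.18; with p = 6/11, 1 − p = 5/11 = 0.45. Each point of difference between the groups then shifts the reported mean by 0.18 to 0.45 points. The documents give no basis for the size of that difference, and without a completion count the reader would not know p either.

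**The case against.** Much of the opposing case is sound.

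- **The sentence may not make adherence the outcome.** The phrase about supporting adherence can describe what partners are there to do, with usability and acceptability as the outcomes, as in the Aim section. A reader might infer that a promised analysis has no outcome variable at all; the text does not establish that. On this milder reading, however, Data analysis still describes nothing by digital literacy or partner status.
- **Some adherence information is collected.** Participants and partners are asked about difficulties in complying, and a partner is a second informant. To say that no adherence data are collected would be wrong. The accurate statement is that no objective measure is named.
- **Some material is not shown.** The bespoke questionnaire has items beyond the two scales, and the topic guide and consent forms are extended data. They may touch on use. Any such questionnaire item would still be self-report, given after completion.
- **Usage records.** A reader might infer that per-user records are there for the taking. The Intervention section shows that diary entries feed the programme, not that investigators can see them.
- **Uptake.** The Recruitment section says "Consecutive patients who meet eligibility criteria will be invited to participate in the study", which supplies the frame for counts of invited and declined patients. Reporting those counts is routine participant flow, and refusal may reflect research burden as much as the acceptability of the programme. This is secondary and is not pressed here.
- **Design intent.** The study describes itself as mixed-methods and qualitative, so self-reported experience is the intended construct. That is fair, but the stated purpose of finding out who can use the programme also needs to know who finished it.

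**Conclusion.** The point holds as a mismatch between a stated analysis and the sections meant to deliver it. The article names no objective completion or usage measure and no analysis by digital literacy or partner status; it reaches adherence only through self-report after completion; and it is silent on people who stop early. It does not hold as a claim that adherence is ignored or that the main aim fails.

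The size is moderate. No number in the article is wrong. What is at risk is the interpretability of the mean scores and the absence of a completion rate, which 20 to 30 participants could estimate to about 56–94% or 61–92% if 80% completed. The conclusion assumes that the unseen questionnaire and extended data do not already supply session counts and an assessment of early stoppers. If they do, the remaining step is to say so in the article and add the description by the two factors.

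**What to change.** **Data collection.** For every enrolled participant, record sessions completed (0 to 6) and the date of last use. Take these from the programme record or, if no export is available, from the participant's progress display at the final contact. State that the questionnaire and interview are also given to those who stop early, and mark those responses as coming from non-completers.

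**Data analysis.** Report completion over all enrolled with an exact 95% confidence interval. Describe sessions completed, System Usability Scale and UMUX-Lite scores by digital literacy and by partner status. With 20 to 30 participants, and partners present by availability rather than allocation, keep this descriptive.

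**Discussion.** Word the sentence so that it is clear whether adherence is an outcome or only the partner's role.

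**Cost.** A small data request or a look at the progress screen, contact with early stoppers, and possibly a consent line; the consent forms are not shown, so whether one is needed cannot be judged here. All of this assumes the record can be exported or viewed. Counts of invited and declined patients can be added as ordinary flow reporting.

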## Conclusion

This mixed-methods analysis of the usability and acceptability of a dCBT-I (
*Sleepio*) intervention in people with cognitive impairment will help inform the design of a future randomised controlled trial that will assess the effectiveness of the intervention in this population.

## Ethics & consent statement

This mixed-methods qualitative study will be conducted in accordance with the Declaration of Helsinki. Ethical approval for this study was granted by the Clinical Research Ethics Committee of the Cork Teaching Hospitals (CREC) on the 5
^th^ December 2023, under CREC reference number: ECM 4 (gg) 05/12/2023. Results of the study will be published in a peer-reviewed journal and presented at relevant academic conferences. Fully informed written consent will be obtained from each participant prior to enrolment.

## Data Availability

No data are associated with this article. Open Science Framework: A protocol for a mixed-methods analysis of the usability and acceptability of a digital cognitive-behavioural therapy for insomnia (dCBT-I) intervention (
*Sleepio*) in participants with cognitive impairment. https://doi.org/10.17605/OSF.IO/U8CBY This article contains the following extended data
^
61
^: Interview Topic Guide Participant Information Leaflet & Consent Form (Participant) Participant Information Leaflet & Consent Form (Study Partner) Open Science Framework: A protocol for a mixed-methods analysis of the usability and acceptability of a digital cognitive-behavioural therapy for insomnia (dCBT-I) intervention (
*Sleepio*) in participants with cognitive impairment. https://doi.org/10.17605/OSF.IO/U8CBY This article contains the following reporting guidelines
^
61
^: Standards for Reporting Qualitative Research Data are available under the terms of the Creative Commons Zero "No rights reserved" data waiver (CC0 1.0 universal).
